**Secondary Efficacy Endpoints will include:**

- ASAS20 response rate
- Mean change in each of the following domains:
  - VAS patient global assessment
  - VAS pain score
  - Bath AS functional index, BASFI
  - Bath AS global index, BAS-G
  - BASDAI –two morning stiffness-related scores
- Patient global assessment, physician global assessment, nocturnal and total back pain, the BASFI and its independent components, and the BASDAI and its independent components.
- Spinal mobility measured with modified Schober’s test, chest expansion, and occiput-to-wall measurement.
- Patients’ preference scale.
- Quality of life as ASQoL questionnaire.
- Laboratory assessment of inflammation with HS-CRP, Immunoglobulin A and ESR
- Serum creatinine、ALT (SGPT)、CBC

**Safety Evaluation** All patients who receive at least 1 dose of test medicine will be evaluated for safety. The following variables will be assessed: physical examination/vital signs, haematology and chemistry profiles, urinalysis, assessment of extra-spinal and extra-articular involvement, premature withdrawal, adverse events, and serious adverse events during the study.

**Statistical Analysis** Descriptive statistics such as number of observations, mean, median, standard deviation, minimum, maximum and 95% confidence interval will be used to summarize the continuous variables. Frequency and proportion will be used to summarize the categorical variables. The primary analysis will be performed based on the intent-to-treat population. All statistical tests will be two-sided which was evaluated at 5% level significance.

Frequency of dropouts, premature termination of study medication, and withdrawal will be provided and summarized. The last-observation-carried-forward (LOCF) approach will be used to evaluate missing data.

Summary tables for demographic data and baseline characteristics will be provided.

The primary efficacy endpoint is the number of responders as determined by the ASAS Response Criteria for improvement at 20% level at week 8. All patients who withdraw before 8 weeks will be considered non-responders for this endpoint.

Changes (and percentage changes) from baseline at each visit in the individual components of the ASAS Working Group criteria (VAS patient global assessment, VAS physician global assessment, VAS total and nocturnal pain, BASFI, BASDAI and BAS-G), spinal mobility measures, complete joint assessment, evaluation of hip involvement, and laboratory assessments of inflammation will be analyzed by using paired-t test.

The number and percentage of patients who experience adverse events will be summarized. The number and percentage of patients who experience potentially clinically significant changes in laboratory results, and those who discontinue, will be tabulated. Transition tables from baseline for physical examination and laboratory results will be summarized.

**Rationale for Number of Subjects** Assuming that the BASDAI scores of treatment group (μ1) reduced to 2 from 4, and the BASDAI scores of control group (μ0) reduce to 3.5 from 4. A 2-side test was used, with type Ⅰ error () = 0.05, statistical power (1-) = 0.8 and standard deviation (SD) = 2. The expected dropout rate is 10% in this research. Finally, the study required only 14 subjects in each group to achieve 95% power. The targeted sample size for the study was 30 patients. Therefore, the study had  95% power to detect a treatment effect with this sample size.

**Ethical Considerations** This study will be conducted in accordance with applicable laws and regulations including, but not limited to, the International Conference on Harmonization Guideline for Good Clinical Practice (GCP) and the ethical principles that have their origins in the Declaration of Helsinki. The institutional review board (IRB)/independent ethics committee (IEC) must review and approve the protocol and informed consent form (ICF) before any subjects are enrolled. The subject must be consented using the approved ICF before any procedures specified in the protocol are performed.

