**Study Design**

This single-centre, open-labeled randomized controlled study will evaluate the safetyand efficacy of adalimumab in etanercept-treated AS patients. Thirty patients will be enrolled and randomized equally into two arms. The treatment arm will receive adalimumab 40 mg subcutaneously biweekly for 8 weeks. The control arm will continue etanercept 25 mg subcutaneously twice a week for 8 weeks. At week 8, the control arm will be switched to adalimumab 40 mg subcutaneously biweekly for another 8 weeks. Evaluations will be performed at baseline, weeks 4, 8, 12 and 16**.**

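### A 5% level for every test, applied to 112 to 224 paired t-tests, leaves the family of secondary tests without error control (minor)

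*Protocol*

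**What the plan says.** All of this is in the Protocol synopsis and flowchart.

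- **Level.** Statistical Analysis sets one rule for all tests: "All statistical tests will be two-sided which was evaluated at 5% level significance".
- **What is tested.** The same section plans tests of "Changes (and percentage changes) from baseline at each visit in the individual components of the ASAS Working Group criteria". It lists these components as "VAS patient global assessment, VAS physician global assessment, VAS total and nocturnal pain, BASFI, BASDAI and BAS-G", and adds "spinal mobility measures, complete joint assessment, evaluation of hip involvement, and laboratory assessments of inflammation will be analyzed by using paired-t test".
- **What the grouped terms contain.** Secondary Efficacy Endpoints gives "Spinal mobility measured with modified Schober’s test, chest expansion, and occiput-to-wall measurement" and "Laboratory assessment of inflammation with HS-CRP, Immunoglobulin A and ESR". It also names "the BASFI and its independent components, and the BASDAI and its independent components" as endpoints.
- **When.** Study Design: "Evaluations will be performed at baseline, weeks 4, 8, 12 and 16". The Study Flowchart marks ESR and HS-CRP after baseline only at weeks 12 and 16. IgA and the other measures that have a row are marked at all four post-baseline visits. Hip involvement has no row.

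The protocol puts no order on the secondary endpoints, labels none of these tests exploratory, and does not say whether the paired tests are run by arm or on the arms together.

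**The concern.** A 5% level protects one comparison. Here the same level is given to a long list of variables, at every visit, on two scales, and any result below 0.05 may be called significant under the rule as written. With that many tests, some small p-values are to be expected even if no variable moves.

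This matters most if the primary result is null, because readers then turn to the secondary p-values. That is quite possible here. On the protocol's own inputs (a between-arm difference of 3.5 − 2 = 1.5 and an SD of 2), 14 patients per arm give a power of about 0.5. The trial is also open-label with patient-reported scales, so an isolated secondary p-value needs more caution than usual.

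**Working it through.** The protocol states no number of tests and no familywise error rate, so there is no figure of its own to reproduce. The count is built from its text.

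**Step 1: variables.**
- Named components: patient global, physician global, total pain, nocturnal pain, BASFI, BASDAI, BAS-G = 7
- Spinal mobility: modified Schober, chest expansion, occiput-to-wall = 3
- Joint assessment = 1
- Hip involvement = 1
- Laboratory: HS-CRP, IgA, ESR = 3
- Total: 7 + 3 + 1 + 1 + 3 = 15

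**Step 2: variable-visits.** Thirteen variables have four post-baseline visits (hip involvement is assumed to follow the text, at each visit). ESR and HS-CRP have two.
13 × 4 + 2 × 2 = 56

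**Step 3: tests.**

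| Reading | Tests | Expected p<0.05 if nothing changes (× 0.05) |
|---|---|---|
| Both scales, arms pooled: 56 × 2 | 112 | 5.6 |
| Both scales, by arm: 56 × 2 × 2 | 224 | 11.2 |
| By arm, without week-8 BASDAI (2 scales × 2 arms = 4) | 220 | 11.0 |
| By arm, without hip involvement: (56 − 4) × 4 | 208 | 10.4 |

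The expected counts do not depend on correlation between tests. They do assume that each test holds its nominal level. Single BASFI and BASDAI items, ASQoL, ASAS20 and the preference scale are not counted.

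**Step 4: which tests could bear on the switch.** Control patients stay on etanercept to week 8. Their tests at weeks 4 and 8 number 13 variables × 2 visits × 2 scales = 52. That leaves 224 − 52 = 172 tests in patients who have switched. Two of these are week-8 BASDAI in the adalimumab arm.

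**Step 5: chance of at least one p<0.05.** If the tests were independent, it would be 1 − 0.95^m: 0.943 for m = 56, 0.997 for m = 112, and above 0.9999 for m = 224. These are upper figures, because the tests are correlated. The protocol gives no correlations, so they are assumed. Simulation used correlated normal scores with no true change, absolute change only:

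| Correlation between variables | One group, 56 tests (n = 15, correlation between visits 0.6) | Pooled arms (n = 30, week-8 BASDAI left out) | Both arms separately (15 each, week-8 BASDAI left out) |
|---|---|---|---|
| 0.3 | 0.85 | 0.85 | 0.98 |
| 0.5 | 0.74 | 0.76–0.77 | 0.95–0.96 |
| 0.7 | 0.61 | 0.61 | 0.85–0.88 |
| 0.9 | not run | 0.36–0.39 | 0.63–0.67 |

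The ranges in the last two columns come from correlations of 0.5 and 0.8 between visits. Percentage change was left out because it nearly repeats absolute change.

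**The case against.** **The SAP could deal with this.** Ranking and multiplicity rules for secondary endpoints are often left to the SAP, which may exist but is not shown. The level sentence does not claim familywise control and does not rule out a hierarchy. This lowers the severity. It does not remove the point, because the protocol has already fixed a level for all tests and prescribed which tests to run.

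**Several stronger readings are tempting, and the documents do not support them.**
- A reader might infer that the plan specifies 224 secondary tests. It does not say that the paired tests are run by arm. That is the natural reading, since treatment differs between arms to week 8, but it is inferred. Four of the 224 are also week-8 BASDAI, which the Primary Efficacy Endpoint section names as primary, and hip involvement has no flowchart row.
- A reader might infer that any of these p-values could pass as an effect of the switch. The 52 control-arm tests at weeks 4 and 8 cannot, because those patients have not switched.
- A reader might infer that the 5% rate holds for no secondary claim. Each single test keeps its nominal level; only the family lacks control.
- A reader might infer that nothing separates the main result from the rest. The protocol does separate primary from secondary endpoints. It names two different primaries (BASDAI under Primary Efficacy Endpoint, ASAS20 under Statistical Analysis), which is a separate fault.

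**The no-change scenario conflicts with the plan's expectations.** The sample-size section expects BASDAI to fall in both arms (4 to 2 and 4 to 3.5), so some within-arm results could be real changes. That stands. The scenario measures how far small p-values can arise by chance and is not a forecast. A real within-arm change would still not be attributable to the switch by a paired test, and a multiplicity correction would not cure that.

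**Such testing is common in small phase 4 trials.** True, and the error rate of a properly defined primary test is unaffected.

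**Conclusion.** The point holds as a minor one. The protocol gives every test a two-sided 5% level and prescribes 112 paired tests if the arms are pooled, or up to 224 if they are run by arm. With no change in any variable, 5.6 to 11.2 of them are expected below 0.05. For one group on absolute change alone, the chance of at least one is about 85% to 61% at between-variable correlations of 0.3 to 0.7. Those correlations are assumptions. If they were as high as 0.9 and the arms were pooled, the chance would fall to 36% to 39%, still well above 5%. The family of secondary tests has no error control as written.

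**What to change.** 1. Reconcile the two stated primary endpoints, since the level cannot be tied to a primary that is defined in two ways.
2. Replace the sentence on the significance level with one saying that the two-sided 5% level applies only to the week-8 between-arm comparison of the primary endpoint.
3. Amend the paragraph on changes from baseline so that all other endpoints and visits are exploratory. To week 8, while the arms differ in treatment, report between-arm differences with 95% confidence intervals and make no claim of significance. Later visits and within-arm changes are descriptive.
4. Drop the test of percentage change, which duplicates that of absolute change and doubles the count (56 × 2 = 112 per group). Percentage change can still be summarised.

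If secondary claims are wanted, a short fixed order of week-8 endpoints, each tested only if the one before is significant, is an option but not a requirement.

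Cost: an edit to the analysis section in more than one place, with no change to visits, data or patients. The downside is that fewer secondary results may be called significant.

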**Efficacy Evaluation**

**Primary Efficacy Endpoint:**

- The primary endpoint of this study is Bath AS disease activity index (BASDAI) at week 8.

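### Unrestricted LOCF can shift the week-8 BASDAI difference and can enter control-arm etanercept values as week-12 and week-16 outcomes

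*Protocol*

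**What the plan says.** All places are in the protocol Synopsis.

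- Missing data (Statistical Analysis): "The last-observation-carried-forward (LOCF) approach will be used to evaluate missing data". No endpoint, visit or period is excepted in that sentence, and no other method for continuous endpoints and no sensitivity analysis is described.
- Endpoint (Primary Efficacy Endpoint): "The primary endpoint of this study is Bath AS disease activity index (BASDAI) at week 8". The Statistical Analysis paragraph names a different primary endpoint: "The primary efficacy endpoint is the number of responders as determined by the ASAS Response Criteria for improvement at 20% level at week 8". For that one it adds: "All patients who withdraw before 8 weeks will be considered non-responders for this endpoint".
- Population: "The primary analysis will be performed based on the intent-to-treat population".
- Visits (Study Design): "Evaluations will be performed at baseline, weeks 4, 8, 12 and 16".
- Switch (Study Design, repeated under Dosage and Administration, where the half-dose control patients also switch at week 8): "At week 8, the control arm will be switched to adalimumab 40 mg subcutaneously biweekly for another 8 weeks".
- After the endpoint statement, the analysis text has change from baseline, BASDAI included, tested at every visit by a paired t test. Weeks 12 and 16 are therefore covered.
- Dropout (Rationale for Number of Subjects): "The expected dropout rate is 10% in this research". It is not split by arm or by period.

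**The concern.** LOCF assumes that a patient's score stays where it was last seen. The sample-size rationale assumes the opposite: BASDAI falls by 2 points on adalimumab and by 0.5 on etanercept. A week-0 or week-4 score entered as a week-8 score therefore removes part of the assumed fall, and removes more of it in the arm that is expected to fall further. The trial is open-label and only one arm changes drug at week 0, so unequal dropout is plausible and the direction of the shift cannot be known in advance.

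The second problem is specific to this design. In the control arm, weeks 4 and 8 are etanercept visits and weeks 12 and 16 are adalimumab visits. A score carried over week 8 is reported under a drug the patient was not taking when it was recorded. The stated objective is the effect of switching to adalimumab, so those are the estimates that would be contaminated.

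**Working it through.** **Inputs from the protocol.** Week-8 means 2 (adalimumab) and 3.5 (etanercept), both from 4; SD 2; 15 per arm; dropout 10%. The planned difference is 3.5 − 2 = 1.5. The stated 14 per group for 95% power does not reproduce from these inputs (48% by a two-sample t test), but this point does not rest on that figure.

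**Assumed, because the protocol does not say.** When dropout occurs, how it splits by arm, and the share f of the week-8 change already reached at the last observation. Dropouts are taken to follow their arm's mean course.

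**1. Shift in week-8 BASDAI.** Let dT and dC be the proportions missing at week 8 in the adalimumab and etanercept arms. Then

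LOCF difference = [3.5 + dC(1 − f) × 0.5] − [2 + dT(1 − f) × 2]

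| Missing (adalimumab / etanercept) | f = 0 | f = 0.5 | f = 1 |
|---|---|---|---|
| 10% / 10% | 3.55 − 2.20 = 1.35 | 3.525 − 2.10 = 1.425 | 1.5 |
| 20% / 0% | 3.5 − 2.4 = 1.10 | 3.5 − 2.2 = 1.30 | 1.5 |
| 0% / 20% | 3.6 − 2 = 1.60 | 3.55 − 2 = 1.55 | 1.5 |

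With equal 10% dropout the loss is 0 to 0.15 points (0 to 10%). The full-data standard error is 2 × √(2/15) = 0.73, so a shift of 0.075 to 0.15 is about 0.1 to 0.2 standard errors. With unequal dropout the shift changes sign.

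**2. Standard error.** Simulation of 40,000 trials, 15 per arm, SD 2, assuming visit correlation 0.6 and missingness completely at random, 10% per arm:

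- LOCF: reported standard error 0.741 to 0.747; actual SD of the LOCF estimate 0.737 to 0.746.
- Complete cases: reported standard error 0.772 to 0.773.

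The ratios are 0.747/0.772 = 0.968 and 0.741/0.773 = 0.959. LOCF is 3 to 4% below complete-case because carried scores count as week-8 data. It is not below its own sampling SD.

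**3. False positives.** Same simulation, both arms truly falling from 4 to 2, half of dropouts last seen at week 0 and half at week 4 with half the change reached. Rejection is 5.0% with 10% missing in each arm, 6.7% with 20% against 0%, and 8.6% with 30% against 0%. If both arms stay at 4, it is 4.9% with 20% against 0%.

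**4. Carry across the switch.** A control patient whose last score is at or before week 8 gets that score at weeks 12 and 16. Two groups arise:

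- Those who left by week 8 never took adalimumab. If all of the 10% dropout fell by week 8, this is 0.10 × 15 = 1.5, so at most 1 to 2 patients.
- Those who switched and left before week 12 may have taken adalimumab, but the carried score is still from etanercept.

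For ESR and HS-CRP the Study Flowchart schedules only weeks 0, 12 and 16, so the value carried to week 12 would be the week-0 value. The protocol assumes no post-switch means, so the size of this distortion cannot be computed.

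**The case against.** The strongest reply has three parts.

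First, this is one sentence in a synopsis, and an unseen SAP may limit LOCF by period or add sensitivity analyses. That is possible. But the protocol has chosen the method, not left it open, and a SAP that used another would contradict it.

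Second, the effect is small. At the protocol's own dropout rate, equal in both arms, the shift is at most 0.15 points and the false-positive rate stays at 5.0%. This stands, and it limits the weight of the point. Larger effects need unequal dropout.

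Third, ASAS20 at week 8 has its own rule. This also stands: withdrawals before week 8 are non-responders, so the LOCF bias described here does not reach them.

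Three stronger readings are tempting and are not supported:

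- A reader might infer that LOCF understates its own standard error, for instance by √(27/30) = 0.949, or about 5%. That ratio compares LOCF with a complete-case analysis, which is a different estimator. In the simulation LOCF's reported and actual variability agree.
- A reader might take 1.35 as the expected result. It needs the whole 10% to be missing by week 8 and every carried score to be at baseline level, in a 16-week study whose dropout timing is not given.
- A reader might count every control patient who leaves before week 12 as never exposed to adalimumab. Only those gone by week 8 are.

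**Conclusion.** The point holds for BASDAI at week 8 and for control-arm outcomes at weeks 12 and 16. Under equal 10% dropout the week-8 difference lies between 1.35 and 1.5 instead of 1.5, with no bias only if scores have plateaued by the last observation. If 20% are missing in one arm only, it lies between 1.10 and 1.30 (adalimumab arm) or between 1.55 and 1.60 (control arm) for carried scores at or up to half of the week-8 change. Carrying across the switch follows directly from reading the LOCF sentence together with the week-8 switch and the visit-by-visit analysis; unexposed patients number at most 1 to 2 of 15.

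The week-8 figures rest on the protocol's means and on assumed timing and arm split of dropout. The 3 to 4% standard-error gap rests further on missingness completely at random and a visit correlation of 0.6. The method should be changed, but at the planned dropout rate it would not by itself overturn the trial's result.

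**What to change.** - For BASDAI and the other continuous endpoints measured at weeks 0, 4 and 8, replace LOCF with a likelihood-based repeated-measures model that takes all three visits as responses, with a common baseline mean across arms. Use the week-8 arm contrast as the BASDAI result. Treating week 0 as a response keeps patients without any post-baseline score in the analysis, in line with intent-to-treat; a model with only weeks 4 and 8 as responses would drop them. Multiple imputation is an acceptable alternative.
- Keep non-responder imputation for ASAS20 at week 8.
- Add a sensitivity analysis that departs from missing-at-random, for example delta-adjusted imputation. LOCF does not test that assumption and should remain at most a supplementary analysis.
- State that no control-arm value is carried across the week-8 switch, and report the number observed at weeks 12 and 16. This covers ESR and HS-CRP too.

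The cost is a change of analysis wording and a standard model. The scores are already scheduled, so no visit or measurement is added. The small downside is reliance on missing-at-random, which the sensitivity analysis examines.

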**Study Objective**

To determine the safety and efficacy of switch effects to adalimumab in etanercept-treated AS patients.

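### The control arm switches at week 8, but the only stated test at weeks 12 and 16 measures change from week 0, so no test in the protocol isolates that arm's own switch

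*Protocol*

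**What the plan says.** All references are to the protocol synopsis unless stated.

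- **Study Objective:** "To determine the safety and efficacy of switch effects to adalimumab in etanercept-treated AS patients".
- **Study Design:** the control arm first continues etanercept for eight weeks, then "At week 8, the control arm will be switched to adalimumab 40 mg subcutaneously biweekly for another 8 weeks". Dosage and Administration gives half-dose patients the same week-8 switch on a monthly schedule.
- **Visits (Study Design):** "Evaluations will be performed at baseline, weeks 4, 8, 12 and 16". Baseline is listed apart from week 8, so it is week 0.
- **Statistical Analysis:** "Changes (and percentage changes) from baseline at each visit in the individual components of the ASAS Working Group criteria", together with spinal mobility, joint and hip assessments, and "laboratory assessments of inflammation will be analyzed by using paired-t test". No other test is named for these outcomes, and no other reference visit is given.
- **Rationale for Number of Subjects:** control BASDAI is expected to "reduce to 3.5 from 4" and treatment-arm BASDAI to go from 4 to 2, with "standard deviation (SD) = 2".
- **Secondary Efficacy Endpoints:** "Laboratory assessment of inflammation with HS-CRP, Immunoglobulin A and ESR".
- **Study Flowchart:** BASDAI, BASFI, BAS-G, the global and pain scores, spinal mobility, joint assessment and IgA are scheduled at week 8. ESR and HS-CRP are scheduled only at weeks 0, 12 and 16.

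**The concern.** The two arms switch at different times. The treatment arm switches at week 0, so its change from baseline to week 8 is also its change since the switch. The control arm switches at week 8, so its change from baseline at weeks 12 and 16 spans two drugs. The stated rule applies the same reference to both arms at every visit.

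The control arm's second period is a further observation of the switch, in about 15 patients who are moved to adalimumab and assessed twice more. Under the stated rule, a significant result at week 12 or 16 does not show that the switch did anything, because some of the change may already have happened on etanercept. No other test stated in the protocol fills the gap.

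A reader can subtract the mean change at week 8 from the mean change at week 16. That gives a point estimate but not its standard error, which depends on the within-patient covariance and is not part of the stated results.

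**Working it through.** The protocol gives no figure for this analysis, so there is none to reproduce. The check breaks down what the stated test measures and sizes the consequence from the planning values.

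**Inputs from the protocol**
- Control arm n = 15 (design diagram below the Study Flowchart).
- Two-sided 5% level (Statistical Analysis).
- Planned control change in weeks 0-8: 4 - 3.5 = 0.5 BASDAI points. Planned treatment-arm value: 2. SD: 2.

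**Assumptions**
- The protocol does not say whether SD 2 is for a single visit or for a change. Two readings are used.
  - SD of change = 2. SD 2 per visit with correlation 0.5 gives the same value.
  - SD 2 per visit with correlation r = 0.8: SD of change = 2 × √(2(1 - 0.8)) = 1.265.
- The course of the scores after week 8 is assumed in each case below.

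**What the test measures**

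For a control patient, (week 16 - week 0) = (week 8 - week 0, on etanercept) + (week 16 - week 8, on adalimumab).

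With d for change from week 0, Var(week 16 - week 8) = Var(d16) + Var(d8) - 2Cov(d16, d8). The two from-baseline results give the variances but not the covariance.

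**Rejection rates**

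Paired t-test, 14 degrees of freedom, noncentrality = mean change / (SD of change / √15).

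| Case | Reference | Mean fall | Noncentrality (SD 2; SD 1.265) | Significant in (SD 2; SD 1.265) |
| --- | --- | --- | --- | --- |
| (a) No switch effect, flat after week 8 | Week 0 | 0.5 | 0.97; 1.53 | 14.7%; 29.7% |
| (a) | Week 8 | 0 | 0; 0 | 5%; 5% |
| (b) No switch effect, a further 0.5 of drift | Week 0 | 1.0 | 1.94; 3.06 | 43.8%; 81.2% |
| (b) | Week 8 | 0.5 | 0.97; 1.53 | 14.7%; 29.7% |

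With n = 14, case (a) from week 0 gives 14.0% to 27.8%.

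**Share of the reported change that precedes the switch**
- Case (a): 0.5 / 0.5 = 100%. Relative to the starting value, the fall is 0.5 / 4 = 12.5%.
- Case (c), switch takes the mean from 3.5 to 2: fall from week 0 = 4 - 2 = 2.0; fall from week 8 = 3.5 - 2 = 1.5; share before the switch = 0.5 / 2.0 = 25%. With SD of change 2, power is 95% from week 0 and 77% from week 8, so the week-8 test keeps useful power for an effect of the planned size.

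**The case against.** The strongest reply is that this is an omission and not a mistake. Change from baseline at each visit is a legitimate quantity, correctly described. Nothing in the protocol says that baseline is the only permitted reference, and an analysis plan that is not shown could add a contrast from week 8. The protocol also names no between-arm test, although the week-8 endpoints and the two-group planning values imply one, so its list of tests may be incomplete. Nowhere does it say that the control arm's week 12 or 16 change will be read as a switch effect. The sponsor will hold patient-level data and can compute the paired difference whenever it likes.

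Much of this stands. Baseline is the only reference *stated*, which is not the same as the only one allowed. The standard-error limit binds a reader of the tables, not the sponsor. The harm arises only if the result is read as the effect of the switch.

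It does not remove the point. The protocol is not silent on the post-switch visits: it assigns them a reference, and that reference does not isolate what the objective asks about. Settling a better reference now also avoids choosing one after the data are seen.

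A reader might infer from the 15% to 81% that the stated test has an inflated type I error. It does not. Those rates are power to detect a real change since week 0. A reader might also take the week-8 reference to identify the drug effect. Case (b) shows otherwise: with continuing drift and no switch effect, it still rejects in 15% to 30% of trials.

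**Conclusion.** The point holds in a limited form. As stated, the control arm's week 12 and 16 results combine etanercept-period change with post-switch change, and no test in the protocol separates them. On the planning values the etanercept part is 0.5 BASDAI points: all of the reported fall if the switch does nothing and scores stay flat, and a quarter of it if the switch achieves the planned treatment-arm value. In the flat case the from-baseline test would be significant in about 15% to 30% of trials, against 5% with a week-8 reference.

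The 0.5, the SD of 2 and n = 15 are the protocol's own. The meaning of the SD, the correlation of 0.8 and the course after week 8 are assumptions.

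A reader might infer that the trial's main result is compromised. The documents do not support that. Both statements of the primary endpoint are at week 8, before the control arm switches, and the treatment arm's week 0-8 change is already a post-switch change. What is affected is a secondary, uncontrolled, open-label period in about 15 patients. This is a free improvement.

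**What to change.** Add one sentence to Statistical Analysis: for the control arm, changes from week 8 to weeks 12 and 16 are the post-switch analysis, by paired t-test, for the measures scheduled at week 8 (BASDAI, BASFI, BAS-G, global and pain scores, spinal mobility, joint assessment and IgA). Label it uncontrolled and open-label, because it removes only change that occurred before week 8. Keep that arm's week 12 and 16 changes from baseline as descriptive results.

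State that ESR and HS-CRP have no week-8 value and are reported from baseline only.

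The cost is wording alone. The week-8 values are already scheduled, and no extra visit, sample or patient is needed.

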# SYNOPSIS

**Study Title**

Etanercept versus Adalimumab in the Treatment of Patients with Ankylosing Spondylitis.

A Switch Study.

**Clinical Phase** 4

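### The only test named for BASDAI and the other continuous measures is a within-patient paired t test, which gives no adalimumab-versus-etanercept contrast

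*Protocol*

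**What the plan says.** The title frames a comparison of two drugs: "Etanercept versus Adalimumab in the Treatment of Patients with Ankylosing Spondylitis". Study Design sets up a concurrent control: "Thirty patients will be enrolled and randomized equally into two arms". Controls stay on etanercept until week 8 and then switch to adalimumab.

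The efficacy section states: "The primary endpoint of this study is Bath AS disease activity index (BASDAI) at week 8". The Statistical Analysis section gives a different primary endpoint, ASAS20 responders at week 8, and names no test for it.

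The continuous measures are covered by one sentence under Statistical Analysis. Its subject is "Changes (and percentage changes) from baseline at each visit in the individual components of the ASAS Working Group criteria". It lists BASDAI, BASFI, BAS-G, the global and pain scales, spinal mobility, joint and hip assessments and inflammation markers, and ends: "laboratory assessments of inflammation will be analyzed by using paired-t test".

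The only general rule on testing is "All statistical tests will be two-sided which was evaluated at 5% level significance". Rationale for Number of Subjects sets a treatment-group BASDAI against a control-group BASDAI ("reduced to 2 from 4, and the BASDAI scores of control group", the latter falling to 3.5 from 4). It refers to a two-sided test without naming it.

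**The concern.** A paired t test of change from baseline asks whether the mean change within a group of patients differs from zero. It uses no information from the other arm. Randomisation protects only the comparison between arms. A within-arm change also contains regression to the mean, ordinary fluctuation and, in an open-label study with a patient-reported score, expectation. The protocol itself expects 0.5 points of improvement in patients who stay on etanercept.

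The protocol is not simply silent here. It assigns a test to change in BASDAI at each visit, week 8 included. That test fits neither the randomised design nor the treatment-versus-control contrast used for sizing. If it were followed as the efficacy analysis, the whole within-arm change could be reported as the effect of switching. Readers would then be left to compare two separate p-values, which is not a test of the difference between arms.

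**Working it through.** **Inputs from the protocol** (Study Design; Statistical Analysis; Rationale for Number of Subjects): 15 per arm; two-sided 5%; treatment BASDAI 4 to 2; control BASDAI 4 to 3.5; SD = 2, with no statement of whether this is the SD of the score or of the change.

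**Assumed inputs:** SD of change 1.5 to 2; baseline-to-week-8 correlation ρ of 0.5 to 0.7.

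**1. Within-arm change against between-arm effect**
- Adalimumab change: 4 − 2 = 2.0.
- Control change: 4 − 3.5 = 0.5.
- Between-arm effect: 2.0 − 0.5 = 1.5.
- Ratio: 2.0 / 1.5 = 1.33. The paired analysis of the adalimumab arm estimates a quantity one third larger than the randomised effect, and 0.5 / 2.0 = 25% of it also occurs in controls.

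**2. What separate paired tests would show if the drugs did not differ**

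Let both arms truly improve by 0.5, the protocol's own control figure. Paired power p comes from the noncentral t with 14 degrees of freedom and noncentrality 0.5 / (SD/√15). The chance that adalimumab is significant and etanercept is not is p(1 − p).

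| SD of change | p | p(1 − p) |
|---|---|---|
| 1.5 | 0.225 | 0.225 × 0.775 = 0.17 |
| 2.0 | 0.147 | 0.147 × 0.853 = 0.13 |

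A valid two-sided 5% test between arms would wrongly favour adalimumab 2.5% of the time. The excess depends on the common improvement. With no change in either arm the rate in adalimumab's favour is 0.025 × 0.95 = 2.4%. With a common change of 1.0 and SD 2, p = 0.438 and the rate is 0.438 × 0.562 = 25%, but the protocol gives no basis for a common change of 1.0.

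**3. Power of a between-arm test at 15 per arm, difference 1.5**

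Noncentrality is 1.5 / (s√(2/15)), where s is the relevant SD.
- Unadjusted, s = 2: noncentrality 2.05, power 51% (t).
- ANCOVA, if SD = 2 is the SD of the score: s = 2√(1 − ρ²). At ρ = 0.5, s = 1.73 and power is 63%. At ρ = 0.7, s = 1.43 and power is 79%.
- ANCOVA, if SD = 2 is the SD of the change: the score SD is 2/√(2(1 − ρ)), so s = [2/√(2(1 − ρ))]·√(1 − ρ²). At ρ = 0.5, s = 1.73 and power is 63%. At ρ = 0.7, s = 1.84 and power is about 57%.

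**4. The protocol's stated power**

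The stated 95% power with 14 per group does not reproduce for a two-arm comparison: with difference 1.5 and SD 2 it is 48% (t). A one-sample test of the adalimumab arm's own change of 2.0 with SD 2 gives 93% at n = 14 (t), or 96% by the normal approximation.

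**The case against.** **A between-arm test may be in the statistical analysis plan, which is not shown.** This stands in part. The rationale contrasts the two groups and mentions a two-sided test, so a between-arm comparison was contemplated. The paired-test sentence does not call itself the primary analysis. The absence of a named test for ASAS20 is therefore not an error in itself. What remains is that the protocol does name a test for change in BASDAI, and that test does not fit the comparison.

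**The paired test has a proper use.** This also stands. The Study Objective speaks of switch effects in etanercept-treated patients, and after week 8 there is no concurrent etanercept arm. Within-patient change is then a natural summary. The mismatch concerns weeks 4 and 8, when the randomised comparison exists.

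**A reader might infer that the trial's false-claim rate is far above 5%.** The documents do not support that as a general statement. It needs a decision rule that appears nowhere in the protocol and a true improvement in both arms.

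**A reader might infer that the sample size was computed from a paired test.** The near match at 14 patients is suggestive, but the protocol gives no formula, so this is conjecture.

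**A reader might infer that baseline adjustment rescues the power.** The 79% needs both ρ = 0.7 and SD = 2 as the SD of the raw score. Under the other reading of SD it is about 57%.

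**Conclusion.** The concern holds as a mismatch between a stated method and the design. The only named test for BASDAI and the other continuous measures contains no arm contrast, so it cannot give the adalimumab-versus-etanercept difference that the control arm exists to provide. It should be corrected before the analysis.

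The overstatement by a third rests only on the protocol's own figures. The 13-17% is an illustration. It rests on a success rule the protocol does not state, on a common improvement of 0.5, and on an assumed SD of change of 1.5 to 2. The power range of 57-79% rests on assumed correlations and an undefined SD. It supports the choice of ANCOVA but is not evidence of the error. The conflict between the two primary endpoints and the unreproduced 95% power are separate matters.

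**What to change.** In Statistical Analysis, state a between-arm analysis of week-8 BASDAI on the intent-to-treat population. ANCOVA on randomised arm with week-0 BASDAI as covariate is preferable, reporting the adjusted difference and its 95% confidence interval. A two-sample t test on change would also be valid but does not use the baseline as efficiently. Adding etanercept dose at entry as a covariate is optional.

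Use the same between-arm approach at weeks 4 and 8 for the other continuous endpoints measured then. ESR and HS-CRP cannot be included: the Study Flowchart schedules them only at weeks 0, 12 and 16, after controls have switched. State a between-arm exact test for ASAS20 response at week 8.

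Keep the paired t tests, labelled as descriptive within-arm summaries, including for the period after week 8. In the rationale, say whether SD = 2 is the SD of the score or of the change.

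The cost is wording only. BASDAI is already collected at weeks 0, 4 and 8, and no extra patients or visits are needed for this change. It does not by itself bring power to 80%; that belongs with the sample-size point.
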